### Objectives:

#### 1. Primary

- a. To investigate the efficacy of prolonged daily VI stimulation
- b. To investigate the safety of prolonged daily VI stimulation
- c. To investigate the efficacy of three different types of stimulation:

|    | Baseline stimulation | Motion-modulation |
|----|----------------------|-------------------|
| 1) | On                   | Off               |
| 2) | On                   | On                |
| 3) | Reduced              | On                |

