#### Endpoints per objective (see above):

1. Primary objectives
  - a. Primary and secondary outcome measures will be compared between conditions with VI stimulation (VI-ON) versus without stimulation (VI-OFF). The primary and secondary outcome measures will also be used to monitor the effect of prolonged stimulation by comparing outcomes at different time points during the prolonged stimulation period.

[figure not shown]

Figure 1: General overview of the VertiGO! trial schedule

- b. Amount of (S)AE's or other undesired side effects (e.g. psychological burden) derived from secondary outcome measures in relation to prolonged daily VI stimulation.
  - c. Primary and secondary outcome measures will be compared between the different stimulation algorithms used during the different prolonged stimulation periods.
- 2. Secondary objectives
  - a. Tailor made rehabilitation programs
  - b. Primary and secondary outcome measures will be used to investigate the interaction between vestibular stimulation and CI functionality
  - c. A subset of primary and secondary outcomes during long-term clinical follow-up up to 5 years

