Risks of vestibular stimulation via the CVI include dizziness, nausea and a risk of falling. The risks of dizziness and nausea will most likely subside as the patient gets more used to vestibular stimulation, and can always be negated by stopping the vestibular stimulation. The risk of falling, alongside any unforeseen risks, is minimized by taking care and time to let the patient get used to vestibular stimulation and by only applying vestibular stimulation while the patient is in the hospital under supervision by a member of the research team. While the patient receives vestibular stimulation via the CVI, the performance of the CI-part of the implant might (temporarily) be reduced.

The benefit for the patient is that via the CI functionality of the CVI their hearing will most likely improve, analogous to a regular CI. The VI functionality of the CVI can only be used within a research setting, and will therefore not result in a direct patient benefit outside of trial related activities under supervision in the hospital.

Concerning group relatedness, BV represents a major handicap with strong balance disturbances, higher risk of falling, visual symptoms (oscillopsia) and a loss of autonomy. There is no therapeutic strategy at the moment. Development of a vestibular prosthesis could help this group of patients to have a better quality of life. With this study we hope to answer crucial research questions (see chapter 1.4 of the research protocol) and bring essential knowledge towards the development and refining of a vestibular prosthesis. This trial is part of a larger plan to develop the concept of a VI which can be adopted into clinics. As described in chapter 1.4, substantial research has been conducted with VI stimulation in the past. This trial serves as the next step in this process. If this trial succeeds in proving the safety and efficacy of prolonged vestibular stimulation, future trials with a larger patient cohort are in the pipeline to build on the knowledge gathered in this trial.

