## 1.3. Vestibulopathy

The importance of the vestibular system's role in body posture, body motion control and perception is often underestimated. Its importance generally becomes clear in motion sickness and after vestibular system failure. The etiology of vestibular loss can be ototoxic, infectious, traumatic, autoimmune, congenital or idiopathic.

Vestibular loss can be divided into two subcategories: unilateral and bilateral loss. Unilateral vestibular loss usually doesn't lead to long term severe symptoms. Plasticity of the central nervous system namely allows efficient compensatory mechanisms to be enforced. In this way unilateral vestibular loss can partly be compensated for, although specific deficits remain . Bilateral vestibular loss, referred to as BV, does often lead to permanent problems.

Patients with BV experience imbalance, disorientation, vertigo and discomfort during all types of movements, leading to impairments and restrictions in functioning during most day-to-day activities. It has been conservatively estimated that >200.000 people in Europe and >2.1 million people worldwide are affected . The prevalence is likely to be underestimated . In absence of treatment options, there is less awareness, inclination and incentive for a formal diagnosis. Other than the obvious burden of disease, BV is associated with reduced societal participation, reduced quality of life (QoL) and a 31x higher risk of falling .

Although progress is being made with devices specifically targeting certain deficits caused by BV, such as sensory substitution devices to help impaired balance , or devices which apply noisy electrical stimulation to enhance residual function , no treatment option to reestablish the full functionality of the vestibular organs exist today. In response to this absence, the concept of a vestibular prosthesis, in analogy with a cochlear prosthesis, is an ongoing and important field of research.

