#### 8.1.1. Main study parameters/endpoints

The primary objective is assessing the efficacy of the CVI in restoring vestibular function. This will be measured by using a set of vestibular tests, of which DVA will be the main outcome parameter. The tests that will be performed observe two vestibular-related reflex pathways: VOR (gaze stabilization) and VSR (postural balance). The VOR tests consist of the DVA test, the functional head impulse test (fHIT), the 3D video head impulse test (3D HIT) and the torsion swing test. All these tests quantify the VOR at different frequencies and at different levels of functionality. The VSR is observed based on gait and balance tests, looking at the full body response to vestibular stimulation on a functional level. Besides these tests, also the threshold of the perception of movement will be measured using the perception platform.

The main comparison will be made between the measurements done during baseline testing (VI-OFF) and the measurements done during the prolonged stimulation period (VI-ON) (see chapter 2). This will give a

Table 6: Overview of VertiGO! objectives, goals, endpoints and outcome parameters

| Objective |                       |    | Goal                          | Measurement points                                   | Outcome parameters |      |                                                                 |
|-----------|-----------------------|----|-------------------------------|------------------------------------------------------|--------------------|------|-----------------------------------------------------------------|
|           |                       |    |                               |                                                      | Type               | Test |                                                                 |
| Primary   | Prolonged daily stim. | 1a | Overall efficacy              | VI-OFF (baseline) vs VI-ON (stim. weeks)             | Prim.              | Main | DVA                                                             |
|           |                       |    | Adaption to stimulation       | VI-ON (start stim. weeks) vs VI-ON (end stim. weeks) |                    | Aux. | fHIT, 3D HIT, Torsion Swing, Gait analysis, Perception platform |

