Each day of CVI stimulation will start and end with impedance measurements and a check of UCLs. This is done as a safety precaution to make sure that the implant is performing as expected, even though it is expected that these parameters will not change during the prolonged stimulation period. These measurements will take only 5 minutes to complete. After this, one hour is reserved on Monday and half an hour on every following day to allow the patient to get used to the stimulation. Previous research by the Geneva-Maastricht group has shown that habituation to stimulation at 50% of the DR takes around 30 minutes for the first time the nerves are stimulated, and progressively less time at the start of each consecutive stimulation period. By taking this time every morning for the patient to get used to the stimulation, the reproducibility of the measurements will increase. At the start of every day the patients will also be asked if any (S)AE's occurred after leaving the hospital the previous day (i.e. attacks of nausea or vertigo). At the end of each prolonged stimulation day, the patients will be asked to fill in the VAS based list of questions to characterize their experiences with the CVI on a daily basis.

All the tests which will be conducted during the prolonged stimulation weeks are shown in table 4 of chapter 3 and described in chapter 8.3.1 through 8.3.5. All testing will occur during the four days of prolonged stimulation, except for three perception tests, one performed each Sunday afternoon before every period of prolonged stimulation. The patient will be asked to arrive in the hospital around 16:00 on Sunday for 1 hour of testing. The patient will be tested while using their regular CI processor. The goal of the tests is to assess if any change occurs in the baseline measurement after the patient has performed the perception platform test a few times. This is to exclude any chance that a learning effect might occur for the perception platform test, which is something that has not yet been fully studied. At the end of this test the patient will also be asked to fill in the VAS based preference scales.

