### 9.2. AEs, SAEs and SUSARs

#### 9.2.1. *Adverse events (AEs)*

Adverse events are defined as any undesirable experience occurring to a subject during the study, whether or not considered related to the experimental intervention or the trial procedure. All adverse events reported spontaneously by the subject or observed by the investigator or his staff will be recorded. Because primary trial objectives involve a safety assessment, the patients will also be actively asked during all trial visits if any AEs occurred.

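### The (S)AE part of primary safety endpoint 1b is a stimulation-week count with no VI-OFF reference, although several expected harms are also symptoms of the disease

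*Protocol*

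**What the plan says.** The Summary lists as a primary objective "To investigate the safety of prolonged daily VI stimulation". The matching endpoint (Endpoints per objective, 1b) is "Amount of (S)AE's or other undesired side effects (e.g. psychological burden) derived from secondary outcome measures in relation to prolonged daily VI stimulation". It has two parts: (S)AEs, and side effects drawn from the secondary outcome measures, which are questionnaires and interviews.

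Table 6 (section 8.1.1) gives overall efficacy (1a) the measurement points "VI-OFF (baseline) vs VI-ON (stim. weeks". For 1b it gives the stimulation weeks only.

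Section 1.3 says of the disease: "Patients with BV experience imbalance, disorientation, vertigo and discomfort during all types of movements". It also cites a 31-fold higher risk of falling. On the intervention, the Summary says: "Risks of vestibular stimulation via the CVI include dizziness, nausea and a risk of falling".

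Section 9.2.1 defines adverse events irrespective of relatedness and adds that "the patients will also be actively asked during all trial visits if any AEs occurred". For the stimulation weeks, section 8.3.6 adds: "At the start of every day the patients will also be asked if any (S)AE's occurred after leaving the hospital the previous day".

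Section 10.2 compares questionnaires at VI-OFF baseline with VI-ON at the end of the stimulation period. Under section 8.3.6 the VAS-based list is completed at the end of the baseline testing day and at the end of each stimulation day.

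**The concern.** A count of events in patients who already have vertigo, imbalance and a raised fall risk mixes disease background with any effect of stimulation. All three randomized periods deliver stimulation, so the cross-over supplies no VI-OFF period for adverse events. The protocol assigns comparators objective by objective and gives this primary objective none for its event count, although section 10 has each subject act as their own control.

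A high count could be read against the device when it is only background. A real increase could equally go unseen, because there is no rate to set it against. Section 11.4.1 makes the planned extension to home use depend on results that favour a safe and effective intervention, so the reading of 1b has consequences.

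**Working it through.** The protocol states no figure for safety, so the check compares passages and then does simple exposure arithmetic.

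**1. Comparators in Table 6**
- 1a, overall efficacy: VI-OFF baseline against the stimulation weeks.
- 1c, stimulation types: week against week.
- 2b, CI and VI interaction: CI on with VI off at baseline, against both on.
- 1b, safety: the stimulation weeks, with no second term.

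**2. Overlap of symptoms**
- Expected harms: dizziness, nausea, falling (Summary).
- Disease: imbalance, disorientation, vertigo, raised fall risk (section 1.3).
- Dizziness and falls overlap. Nausea is an expected harm that section 1.3 does not list as a disease symptom.

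**3. What a stimulation-week count contains**
Section 8.3.6 gives about 8 hours of CVI use per day on 4 days; at all other times the patient uses the regular CI processor without vestibular stimulation. VI-ON time is about 8/24 = 33% of a stimulation day and 4 × 8 = 32 of 7 × 24 = 168 hours (19%) of a calendar week. The morning question quoted above asks about time out of hospital, which is VI-OFF time. A count by week therefore pools ON and OFF hours unless they are separated.

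**4. Exposure**
Fitting 4 + baseline 1 + stimulation 3 × 4 = 17 days, which agrees with the 17 testing days stated under Table 1, at about 8 hours each.
- Stimulation days: 12 × 8 = 96 patient-days; 12 × 13 = 156.
- Baseline testing days: 1 × 8 = 8; 1 × 13 = 13.
- Rest days between the weeks (Friday to Sunday, twice): 6 × 8 = 48; 6 × 13 = 78.

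**5. Illustration with no stimulation effect**
The documents give no background rate. Let b be an assumed share of patient-days with a recorded symptom. Expected event-days = patient-days × b. The chance that a patient has at least one in 12 days is 1 − (1 − b)^12, with days treated as independent.

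| b (assumed) | Stimulation, n = 8 | Stimulation, n = 13 | Baseline day, n = 8 | Baseline day, n = 13 | Patient with ≥ 1 in 12 days |
|---|---|---|---|---|---|
| 10% | 9.6 | 15.6 | 0.8 | 1.3 | 72% |
| 30% | 28.8 | 46.8 | 2.4 | 3.9 | 99% |
| 50% | 48 | 78 | 4 | 6.5 | > 99.9% |

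About 29 event-days among 96 fits a 30% background with no effect (28.8). It fits equally well a 10% background tripled by stimulation (3 × 9.6 = 28.8). The count alone cannot tell these apart.

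**6. How much the baseline day can say**
If no patient has a given symptom on the baseline day, the one-sided 95% upper limit for the background share is 1 − 0.05^(1/8) = 31% with 8 patients and 1 − 0.05^(1/13) = 21% with 13. The reference is useful but imprecise.

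**The case against.** The other side has good points.

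- **Part of 1b already has a VI-OFF comparison.** Section 10.2 provides one for questionnaires, and the VAS list on the severity of vestibular symptoms is completed both at baseline and daily under stimulation. This stands. A reader might infer that safety has no VI-OFF comparison at all, but the documents do not support that.
- **Daily asking does not demonstrably inflate VI-ON counts.** A reader might take the morning question as evidence of inflation. It covers evenings and nights, when vestibular stimulation is off, so it yields VI-OFF data. This stands.
- **The endpoint wording ties events to stimulation, and attribution rules may sit in the analysis plan.** This is partly right, and missing causality criteria are not the point here. The protocol itself, however, fixes the measurement points per objective and leaves 1b without a comparator.
- **The background rates are assumed.** This stands. They also presume that unchanged chronic symptoms would be logged as events, which the protocol does not say. The 31-fold figure is relative and gives no daily rate.
- **Home rest days are a poor control.** They lack the head impulses, rotatory chair, platform and perturbed walking of stimulation days, rely on recall, and serve as wash-out. This stands, so they cannot be the main reference.
- **The trial is small and exploratory.** That argues for description rather than a test. It does not argue against having a reference.

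**Conclusion.** The point holds for the (S)AE part of endpoint 1b and its Table 6 row: as planned, that count cannot separate stimulation effects from disease background for dizziness and falls. It does not extend to the questionnaire part.

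The size cannot be fixed from the documents. Under assumed background shares of 10% to 50% of patient-days, about 10 to 48 of 96 stimulation days (n = 8), or 16 to 78 of 156 (n = 13), would carry an event with no stimulation effect. These figures illustrate the ambiguity and do not estimate it.

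A reader might also infer that an incompletely blinded team would dismiss real harms as disease. Nothing in the protocol suggests this; all that can be said is that the stated endpoint offers no rate against which to check such a judgement. This is an inexpensive improvement to a primary objective, and it does not show that safety monitoring is inadequate.

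**What to change.** In endpoint 1b and its Table 6 row:

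- Keep the full (S)AE listing unchanged.
- Add, for dizziness, nausea and falls, a descriptive within-patient comparison of VI-ON time (supervised hospital hours in the stimulation weeks) with VI-OFF time.
- Make the VI-OFF baseline testing day the main reference, since it has largely the same provocative tests and a similar length of day. Use evenings and nights and the Friday-to-Sunday rest days as supporting references, shown separately.
- Ask the same adverse-event questions at each existing contact, and record whether stimulation was on at onset.
- Report the baseline VAS symptom list against the daily stimulation-week VAS under 1b.

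The cost is one endpoint sentence, one table cell and a uniform set of questions, settled before the first baseline testing day. No visit is added.

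The downside is that each patient has only one baseline day, against 12 stimulation days. Rest days also differ in setting, test provocation, recall and possible after-effects. The comparison should be labelled descriptive and approximate, with no hypothesis test.

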#### Outcome measures:

1. Primary: The main outcome measure is image stabilization based on dynamic visual acuity (DVA). Complementary to the main outcome measure, a set of auxiliary outcome measures are included to assess all functional aspects of combined vestibular and cochlear stimulation. These include a gait analysis to assess locomotion, video-oculography (VOG) to assess gain of stimulation, perception of movement to assess stimulation perception and hearing tests to assess CI functionality.
2. Secondary: Subjective outcomes based on questionnaires and semi-structured qualitative interviews.

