**5.2. Use of co-intervention (if applicable)**

In case of discomfort the CVI processor can be turned off or removed from the patient's head at any point, instantly stopping the stimulation of the vestibular system.

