#### 6.4.6. *Risks related to adjusting the settings of the CVI*

Adjusting the settings of the CVI results in changing the previous stimulation state of the vestibular nerves. Research shows that this can lead to dizziness . By performing the adjustments of the stimulation settings in a gradual fashion, utilizing the adaptive capabilities of the human brain, this dizziness can be kept to a minimum. Additionally, due to the change in balance perception, there is a potential risk of falling. The current set-up of the trial takes these risks into account and attempts to minimize them by

scheduling 4 full days to adjust and fine-tune the stimulation settings. This fitting period specifically focusses on preventing side effects as much as possible. When applied in previous research from the Geneva-Maastricht Group, this way of adjusting the stimulation settings resulted in only mild and temporary side effects (e.g. tiredness).

It has also been shown that side effects decrease with increasing use of the CVI. Previous experiments with a patient who received a CVI showed that the duration of unwanted nystagmus which can cause dizziness decreased substantially within several on-off cycles. This suggests the potential of reaching a situation of dual-state adaptation, where the patient is able to switch the CVI on and off without any side effects.

Since this will be the first time that the CVI will be used for prolonged stimulation while the patient performs daily tasks, there is a chance for side effects such as nausea to occur during this period, in combination with certain stimulation algorithms. Also there is a potential risk of falling due to changes in balance perception. When they occur, these side effects might be reduced by optimizing stimulation settings. These side effects can always be stopped by turning off the AMP or taking off the device. The risks related to these side effects are minimized due to the vestibular stimulation only being applied under supervision within the hospital.

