#### **8.4. Withdrawal of individual subjects**

Patients can leave the study at any time for any reason if they wish to do so without any consequences. The investigator can decide to withdraw a subject from the study for urgent medical reasons.

As stated in chapter 4.2 and 4.3, patients who make use of VOR suppressing medications will either be asked to stop using this medication before joining the trial (in the case of cinnarizine), or will not be included (in the case of psychiatric medication, e.g. benzodiazepines). However, it can occur that the patient will start taking these medications after they have been included in the trial. If this occurs, it will be noted as a confounder due to the potential effect these medications can have on the VOR response. It will not be seen as a reason for the withdrawal of the patient since the use of these medications does not affect the safety of the patient in the trial and excluding a patient is more detrimental to the usability of the overall data than the potential effect VOR suppressing medications might have. The patients will be notified that they have to inform the research team if they start using VOR suppressing medications (see section E of the standard research file).

Pregnancy is also stated as an exclusion criteria for the trial. However, pregnancy will also not be seen as a reason for the individual withdrawal of a patient. If a patient becomes pregnant, all trial activities which might pose a risk to the pregnancy will be postponed or cancelled until after the pregnancy. Postponing or cancelling will have a smaller influence on the usability of the data gathered in this trial than the

outright withdrawal of a patient. By individually changing the trial schedule there will be no risks for the patient or the pregnancy. The patients will be notified that they have to inform the research team in case of pregnancy (see section E of the standard research file).

Due to the novelty of this study, situations might occur which can cause unforeseen discomfort or side effects for the patient. If this occurs, for example caused by certain stimulation algorithms or measurements, the patient will always have the choice to not undergo a certain part of the trial activities. The planning will then be adapted to this patient specifically to decrease the burden on the patient, and this will not necessarily be seen as a reason for individual patient withdrawal.

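### Adverse events are an undivided amount over the stimulation weeks and are left out of the between-algorithm comparison, so the trial would rank algorithms on efficacy without matching adverse-event and tolerability figures

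*Protocol*

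**What the plan says.** The Summary (Endpoints per objective) sets the safety endpoint, 1b, as "Amount of (S)AE's or other undesired side effects (e.g. psychological burden) derived from secondary outcome measures in relation to prolonged daily VI stimulation". Table 6 in section 8.1.1 gives its measurement point as the stimulation weeks, undivided.

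For objective 1c the Summary says "Primary and secondary outcome measures will be compared between the different stimulation algorithms used during the different prolonged stimulation periods". Table 6 sets this out week against week and lists DVA and the auxiliary function tests. The Summary defines the primary outcomes as DVA with auxiliary gait, eye-movement, motion-perception and hearing tests, and the secondary outcomes as "Subjective outcomes based on questionnaires and semi-structured qualitative interviews". (S)AEs are in neither class.

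On harm linked to an algorithm, section 6.4.6 says "there is a chance for side effects such as nausea to occur during this period, in combination with certain stimulation algorithms". Section 8.4 also names algorithms as a possible cause of discomfort, and section 10.4 reserves an extra interim analysis in case one algorithm shows fundamental problems.

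On exposure, section 5.2 says "In case of discomfort the CVI processor can be turned off or removed from the patient's head at any point". Section 8.4 adds that "the patient will always have the choice to not undergo a certain part of the trial activities", which need not lead to withdrawal.

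**The concern.** The order of the algorithms is the only randomised, patient-blinded element of the trial (sections 3.1 and 8.2). As the endpoints are written, that comparison yields figures on function and patient report, but none on (S)AEs or on how often stimulation was stopped or declined. The protocol foresees that harm may depend on the algorithm, yet its adverse-event endpoint is not defined by algorithm.

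The scale matters too. Exposure may be cut short because of poor tolerability, so an amount without a denominator is hard to interpret. The results are meant to inform a later confirmatory trial (chapter 10) and possibly a home-use extension if they look safe and effective (section 11.4.1). A ranking of algorithms without the matching adverse-event figures would be a weak basis for either.

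**Working it through.** **Figures in the protocol.** It gives no adverse-event rate, so there is no safety figure to reproduce. Section 8.3.6 plans about 8 hours a day for 4 days per algorithm, which is 4 × 8 = 32 hours per patient. With 8 to 13 patients (section 4.4) that is 8 × 4 = 32 to 13 × 4 = 52 patient-days per algorithm. All event rates below are assumptions, chosen to show a range.

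**Case 1: one total over the three weeks.** With equal exposure, the total per patient-week is the mean of the three rates.
- Only one algorithm causes events, at rate r: (r + 0 + 0) / 3 = r/3.
- 50% of patients have an event in one algorithm's week and 5% in each of the others: (50 + 5 + 5) / 3 = 20%, which is 50 / 20 = 2.5 times lower than the worst week.

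A single total also cannot show which algorithm the events came from.

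**Case 2: the amount split by algorithm, but without exposure.** Assume that each patient stops the poorly tolerated algorithm at the first event, that the other two run the full 4 days, and that rates are constant.
- Expected events on the poor algorithm: n × (1 − exp(−4 × rate)).
- Stimulated patient-days on it: that count divided by the rate.
- Expected events on each other algorithm: n × 4 × rate.

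For n = 8 and 1.0 against 0.4 events per day:
- Poor algorithm: 8 × (1 − exp(−4)) = 7.9 events in 7.9 / 1.0 = 7.9 patient-days.
- Each other algorithm: 8 × 4 × 0.4 = 12.8 events in 32 patient-days.

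Simulation gave the probability that the poor algorithm shows strictly the fewest events:

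| Events per day, poor vs others | Expected events, n = 8 | Probability, n = 8 | Probability, n = 13 |
|---|---|---|---|
| 1.0 vs 0.1 | 7.9 vs 3.2 | 0.00 | 0.00 |
| 1.0 vs 0.3 | 7.9 vs 9.6 | 0.41 | 0.51 |
| 1.0 vs 0.4 | 7.9 vs 12.8 | 0.81 | 0.92 |
| 1.5 vs 0.5 | 8.0 vs 16.0 | 0.96 | 0.99 |

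Reversal therefore needs a fair number of events on the other algorithms. It does not occur when those are rare, unless the week is declined altogether, in which case it contributes no events.

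**The same 1.0 vs 0.4 example with the proposed figures (n = 8).**
- Events per stimulated patient-day: 7.9 / 7.9 = 1.0 against 12.8 / 32 = 0.4.
- Patients with at least one event: 7.9 of 8 against 8 × (1 − exp(−1.6)) = 6.4 of 8.
- Weeks cut short: 7.9 of 8 expected against none.

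All three put the algorithms in the right order.

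**The case against.** The strongest reply is that this belongs in the statistical analysis plan. Chapter 10 calls itself an outline, a definitive plan is to follow, and nothing forbids a table by algorithm. That holds for table layout and the choice of denominator, and it keeps the weight of the point low. It does not answer the whole point, because the protocol itself fixes what 1b measures and what 1c compares, and (S)AEs are outside 1c.

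Several stronger readings are tempting, but the documents do not support them.
- **The protocol orders pooling.** It does not. This is inferred from the wording of 1b and the undivided entry in Table 6, whose layout is damaged in the text at hand.
- **There is no safety comparison between algorithms.** Too strong. Endpoint 1b itself counts side effects derived from secondary outcomes, and 1c compares those. Daily VAS questions, interviews and end-of-period questionnaires run in every algorithm week.
- **The protocol expects algorithm-specific harm.** It speaks only of a chance, and section 2.1 expects stimulation to be safe.
- **Harm would be both diluted and reversed.** These belong to different reports. A single total has no per-algorithm count to reverse, and a split has nothing to dilute.
- **Stopping after day 1 leaves a quarter of the events.** It leaves 8 / 32 = 25% of the exposure. The same share of events needs a constant rate, whereas the Summary and section 6.4.6 suggest that side effects fade with use. Early clustering would also weaken the reversal in case 2. Discomfort that makes a patient stop is itself an adverse event under section 9.2.1.

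It is also fair that 8 to 13 patients and descriptive comparison (section 10.1) mean that no formal decision hangs on the total.

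**Conclusion.** The point holds as a cheap improvement. As written, (S)AEs are one amount over the stimulation weeks and are not among the outcomes compared between algorithms. Stopped or skipped stimulation is not reported by algorithm either.

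If a single total is reported, harm confined to one algorithm appears at about one third of that algorithm's rate per patient-week, assuming equal exposure. If the amount is split without exposure, a poorly tolerated algorithm can be understated, and under some assumed rates it shows the fewest events. Whether that happens depends on event rates and stopping behaviour, which the protocol does not give. The gap does not extend to side effects captured by questionnaires and interviews.

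**What to change.** In endpoints 1b and 1c and in Table 6, state that (S)AEs are reported descriptively by the algorithm assigned to that week, as:
- patients with at least one event;
- events per stimulated patient-day.

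Report switch-offs, shortened days and declined weeks due to side effects by assigned algorithm as a tolerability outcome.

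The cost is a few lines of wording and one table. Patients are asked about events every stimulation day, and one algorithm is used per week (section 8.3.6), so events can be placed. Stimulated time has to be logged where a day is cut short. With 8 to 13 patients the figures are descriptive only, in line with section 10.1. No change to stopping, skipping or any other clinical management is proposed.
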